## Abstract

**Background:**

Fatigue is a major problem of cancer patients. Thirty percent of cancer survivors report serious fatigue three years after finishing treatment. There is evidence that physical exercise during cancer treatment reduces fatigue. This may also lead to an improvement of quality of life. Such findings may result in a decrease of healthcare related expenditures and societal costs due to sick leave. However, no studies are known that investigated these hypotheses. Therefore, the primary aim of our study is to assess the effect of exercise during cancer treatment on reducing complaints of fatigue and on reducing health service utilisation and sick leave.

**Methods/Design:**

The Physical Activity during Cancer Treatment study is a multicentre randomised controlled trial in 150 breast and 150 colon cancer patients undergoing cancer treatment. Participants will be randomised to an exercise or a control group. In addition to the usual care, the exercise group will participate in an 18-week supervised group exercise programme. The control group will be asked to maintain their habitual physical activity pattern. Study endpoints will be assessed after 18 weeks (short term) and after 9 months (long term). Validated questionnaires will be used. Primary outcome: fatigue (Multidimensional Fatigue Inventory and Fatigue Quality List) and cost-effectiveness, health service utilisation and sick leave. Secondary outcome: health related quality of life (European Organisation Research and Treatment of Cancer-Quality of Life questionnaire-C30, Short Form 36 healthy survey), impact on functioning and autonomy (Impact on functioning and autonomy questionnaire), anxiety and depression (Hospital Anxiety and Depression Scale), physical fitness (aerobic peak capacity, muscle strength), body composition and cognitive-behavioural aspects. To register health service utilisation and sick leave, participants will keep diaries including the EuroQuol-5D. Physical activity level will be measured using the Short Questionnaire to Assess Health-Enhancing Physical Activity and will be monitored with an exercise log and a pedometer.

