## Methods/Design

### Design

The PACT-study examines the effects of exercise during cancer treatment on reducing complaints of fatigue and in reducing health service utilisation and sick leave (primary outcomes). In addition, we will study the effects on improving health related quality of life, impact on autonomy and participation, anxiety and depression, physical fitness, body composition and cognitive-behavioral aspects (secondary outcomes). This study is designed as a multicentre pragmatic randomised controlled trial, with two study arms, i.e. a group invited for an exercise programme in addition to usual care; and the control group receiving usual care while maintaining their habitual physical activity pattern. The exercise programme is an 18-week supervised group programme. Because blinding of participants towards allocation is not feasible, this study has a pragmatic design.

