#### Primary outcomes

Fatigue will be measured using the Multidimensional Fatigue Inventory (MFI) and the Fatigue Quality List (FQL) [24,25]. The MFI is a 20-item self-report instrument designed to measure multiple fatigue characteristics and the impact on function. The Dutch version of the MFI has proven to be valid and consists of five subscales (general fatigue, physical fatigue, reduced activity, reduced motivation and mental fatigue) [24].

The FQL consists of 28 adjectives addressing the perception of fatigue [25]. Participants are asked to mark which out of 28 adjectives fit their experienced fatigue. Multiple answers are possible. The adjectives are clustered in four subscales: frustrating, exhausting, pleasant and frightening.

To register health service utilisation and sick leave participants will keep diaries. Diaries will include all types of health care consumption also including contacts with alternative medicine and own out of pocket expenses. Participants will be asked to keep track of their absence from work (if applicable).

The diaries include also a multidimensional measurement of health status, the EuroQuol-5D (EQ-5D). The EQ-5D will be used to calculate quality adjusted life years (QALYs) and consists of the EQ-5D descriptive system and the EQ VAS [26]. The EQ-5D descriptive system comprises five dimensions of health (mobility, self-care, usual activities, pain/discomfort anxiety/depression). Each dimension comprises three levels (no problems, some/moderate problems, extreme problems). The EQ VAS records the respondents self-rated health status on a vertical graduated (0-100) visual analogue scale.

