### Sample size

In accordance with previous studies [34], we consider an effect of a 2-unit improvement in the MFI questionnaire to be clinically relevant. To detect an intervention effect of 2 units of change (± SD 4) in fatigue (MFI questionnaire (range subscale 4-20)) we will need 75 participants in the intervention and control group for each cancer type, 300 participants in total (alpha = 0.05, power = 0.80). A drop-out of 10% is anticipated. The proposed number of participants also allows us to perform analyses for the two types of cancer separately.

This sample is also large enough to detect a clinically relevant intervention effect of 10 units of change (± SD 20) on the secondary outcome EORTC QLQ C30 subscales [35].

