### Data analysis

Descriptive statistics will be used to characterise the study population and the instrument scores at baseline and at the follow up measurements. Mean differences including 95% confidence intervals will be calculated. Mean differences will be presented for the total study population and for different subgroups (cancer type, cancer regime). The effect of physical exercise on fatigue will be tested at 18 weeks (end of the exercise programme) and nine months post-enrolment according to the intention to treat principle (primary analyses), and on a per protocol basis including participants of the exercise group who attended at least 75% of the exercise sessions. Longitudinal analyses will be conducted, using mixed linear regression models while taking different levels (time and hospital) into account [35]. In the longitudinal analyses the programme accounts for missing data based on the observed data.

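### Fatigue is primary on nine subscales at two visits, but the stated alpha and power belong to one unnamed MFI subscale at one unnamed visit

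*Protocol article*

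**What the plan says.** The abstract lists the primary outcomes without ranking them: "Primary outcome: fatigue (Multidimensional Fatigue Inventory and Fatigue Quality List) and cost-effectiveness, health service utilisation and sick leave". The Design section also names several, saying that the study examines effects "on reducing complaints of fatigue and in reducing health service utilisation and sick leave (primary outcomes"; unlike the abstract, it does not list cost-effectiveness there.

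Under Primary outcomes, the MFI "consists of five subscales (general fatigue, physical fatigue, reduced activity, reduced motivation and mental fatigue", and for the FQL: "The adjectives are clustered in four subscales: frustrating, exhausting, pleasant and frightening". No total score and no leading subscale is given for either instrument.

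The Data analysis section says: "The effect of physical exercise on fatigue will be tested at 18 weeks (end of the exercise programme) and nine months post-enrolment". It marks the intention-to-treat analysis as primary, also specifies mixed models over time, and presents mean differences for the total population and for subgroups that include cancer type.

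The Sample size section takes a 2-unit change with SD 4 on an MFI subscale scored 4 to 20. It asks for 75 patients per arm per cancer type, "300 participants in total (alpha = 0.05, power = 0.80", and anticipates 10% dropout. It does not say which subscale or which visit. The Discussion says that power was calculated for each cancer site separately.

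**The concern.** A single alpha and a single power figure describe a single test. Here the primary fatigue outcome can be read as nine subscales at two visits, and the article does not say which result would decide whether exercise reduces fatigue. A favourable result on any one subscale, at either visit, could then be presented as a positive primary result, at a false-positive rate well above the stated one.

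Two features add to the risk. Participants know their allocation and fatigue is self-reported, so the choice among scales should be closed before results by arm are seen. The article also ties a consequence to the result: if exercise proves effective and cost-effective, standardised programmes are to follow. Which fatigue result counts as effective is left open.

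**Working it through.** **Count of comparisons.** Five MFI plus four FQL subscales = 9. Times two visits = 18. For the MFI alone, 5 × 2 = 10.

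**The plan's own figure.** Inputs from Sample size: difference 2, SD 4 (standardised difference 0.5), alpha 0.05 (taken as two-sided, since sidedness is not stated), power 0.80.

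- n per arm = 2 × (1.960 + 0.842)² × 4² / 2² = 62.8, so 63 (64 by t test).
- With 10% dropout: 63/0.9 = 70, or 64/0.9 = 71.1, so 72. The plan's 75 is slightly generous.
- Completers: 75 × 0.9 = 67.5 per arm within one cancer type. Power by t test is 0.82.

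The stated figures are therefore sound for one MFI subscale, at one visit, in one cancer type.

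**False-positive rate with no effect, each test at two-sided 0.05.** If the tests were independent: 1 − 0.95^18 = 0.60 for 18 tests and 1 − 0.95^10 = 0.40 for ten. Subscales and visits are correlated, so I simulated correlated normal test statistics, with |z| > 1.96 counted as significant. Assumptions, none given in the article: correlation r between subscales, 0.5 between visits, and the product of the two for different subscales at different visits.

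| r | 18 tests, either direction | 18 tests, favouring exercise | 10 MFI tests, either direction | 10 MFI tests, favouring exercise |
|---|---|---|---|---|
| 0.3 | 0.52 | 0.27 | 0.35 | 0.18 |
| 0.5 | 0.44 | 0.23 | 0.31 | 0.16 |
| 0.7 | 0.34 | 0.17 | 0.26 | 0.13 |

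The nominal rate is 0.05 in either direction and 0.025 favouring exercise. At r = 0.9 the 18-test rate favouring exercise is still about 0.11. If only one visit is counted (nine tests), the either-direction rate is 0.33 to 0.20 for r = 0.3 to 0.7.

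**Power if alpha is split instead.** With n per arm, the expected z is 0.5 × √(n/2): 2.905 at n = 67.5 (one cancer type) and 4.108 at n = 135 (both types pooled, 150 × 0.9). Power is approximately Φ(expected z − critical z); the last two columns give the t-test values.

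| Bonferroni over | alpha per test | critical z | one cancer type | pooled |
|---|---|---|---|---|
| 1 test | 0.05 | 1.960 | 0.82 | 0.98 |
| 10 tests | 0.005 | 2.807 | 0.52 | 0.90 |
| 18 tests | 0.0028 | 2.991 | 0.45 | 0.86 |

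For example, with ten tests in one cancer type, Φ(2.905 − 2.807) = Φ(0.098) = 0.54, and the t test gives 0.52.

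**The case against.** Several points on the other side are fair.

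- **The count of 18 is inferred.** The article does not say that each subscale at each visit is a separate confirmatory test, and a mixed model could combine the visits. This stands as a condition on the figures. But fatigue is said to be tested at both times, and even nine tests at one visit give 0.20 to 0.33.
- **The sample size points to the MFI.** This is a partial anchor. It leaves five subscales and two visits open, and the abstract and the Primary outcomes section still put the FQL beside the MFI.
- **A full protocol or analysis plan may hold a multiplicity rule.** It may, and the absence of one from a condensed article is not the point. The point is what the article fixes: several equal primary outcomes beside one alpha and one power figure whose test is not identified.

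Some stronger readings are tempting but not supported.

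- A reader might infer that correcting for multiplicity destroys the power of the trial. That is so only for claims within one cancer type; pooled power stays above 0.80 even with Bonferroni over all 18 tests.
- A reader might count total, breast and colon results as 54 primary tests. The Data analysis section presents the cancer types as subgroups, so that count treats descriptive results as confirmatory.
- A reader might add the economic outcomes to the error count. The economic sections rely mainly on estimation (costs, QALYs, incremental ratios) and specify no hypothesis test. The Discussion's requirement of effective and cost-effective is a joint condition, which does not inflate alpha.
- A reader might quote the either-direction rates as the chance of a false claim of benefit. About half of those results would favour control.

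**Conclusion.** The point holds. The stated alpha of 0.05 and power of 0.80 describe one MFI subscale at one visit, and the article does not say which, while the primary fatigue outcome spans nine subscales and two visits.

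If all 18 comparisons are tested at 0.05, the chance of at least one false significant result favouring exercise is about 17% to 27%, or 34% to 52% in either direction. For the MFI alone it is 13% to 18%, or 26% to 35%. These ranges rest on assumed correlations and on separate testing of each subscale at each visit. Their size is uncertain, but the rate stays well above nominal across the correlations tried.

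The loss of power under a Bonferroni split is serious within one cancer type (0.52 over ten MFI tests), which is the comparison that the Discussion says was powered. It is modest in the pooled population (0.90). The sample size is adequate for its own single test; the defect is that this test is never identified.

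**What to change.** Before any outcome data are examined by arm:

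1. Name one MFI subscale at one visit, for example general fatigue at 18 weeks, as the confirmatory fatigue test at two-sided 0.05.
2. Test the same subscale at nine months next in a fixed sequence, only if the first test is significant. This costs no alpha.
3. Make the other MFI subscales and the FQL secondary.
4. Keep health service utilisation, sick leave and cost-effectiveness as a separate economic objective, reported by estimates and intervals, and state that the trial was not sized for them. Error control does not require demoting them, and doing so would remove part of the declared primary aim.

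The first test then has the stated alpha, and power of about 0.82 within each cancer type after 10% dropout. The cost is a change of wording in the protocol and registry, with no added patients or data. The downside is that effects on the other fatigue subscales can no longer be claimed as primary results.

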**Discussion:**

This study investigates the (cost)-effectiveness of exercise during adjuvant treatment of patients with breast or colon cancer. If early physical exercise proves to be (cost) effective, establishing standardised physical exercise programmes during cancer treatment will be planned.

**Trial registration:**

Current Controlled trials ISRCTN43801571, Dutch Trial Register NTR2138

## Background

With the rising number of cancer survivors, there is an increasing awareness of maintaining optimal health in this group. Although treatment of other cancer- or treatment-related symptoms such as nausea and pain has improved considerably during the last decades, there is still no accepted treatment for complaints of fatigue. Sixty to 96% of (former) cancer patients report complaints of fatigue during and/or after treatment [1,2]. Although levels of fatigue decrease gradually in disease-free survivors, 30% of cancer survivors still report serious complaints of fatigue three years after completion of medical treatment [3]. Fatigue is expected to lead to decreased quality of life, decreased levels of physical activity and increased episodes of sick leave and production loss. For instance, in 2005, in the Netherlands 22.000 persons were unfit for work due to current or previous cancer [4].

The cause of fatigue in cancer patients and survivors is unknown: it may be caused by the disease itself, its treatment or it may be the result of psychological and physiological responses [2]. Deconditioning due to further reduction of physical activity in cancer patients might even further affect feelings of fatigue [5]. The National Comprehensive Cancer Network, an alliance of 21 of the world's leading cancer centres, advises to start physical exercise shortly after cancer diagnosis [6]. Several studies, mainly small scaled and in breast cancer patients, have shown that exercise during cancer treatment prevents complaints of fatigue and improves quality of life [7-13]. A Cochrane meta-analysis recently provided evidence that exercise is beneficial in the management of cancer-related fatigue, also during cancer treatment [12]. The meta-analysis includes physical exercise during or after cancer treatment, in adults, regardless of gender, age, tumour type, tumour stage or type of cancer treatment. Interventions took place in different settings and included all types of exercise (supervised as well as home-based exercise and aerobic as well as resistance exercise). We published a meta-analysis assessing effects of different exercise prescription parameters during adjuvant treatment on cancer related fatigue with special emphasis on safety and feasibility of exercise during adjuvant treatment [13]. Significant beneficial effects were visible for exercise during breast cancer treatment (supervised aerobic), adherence was moderate to excellent and few adverse events occurred.

However, cost-effectiveness of such programmes has not been studied before. We hypothesise that an early start of physical exercise during treatment will lead to a decrease in health care related expenditures by reducing healthcare utilisation. Especially reductions in the number of visits to medical specialists, general practitioners and from home care workers are expected.

We further anticipate that the beneficial effect on healthcare related expenditures is present during the exercise programme, and that it will continue to exist after termination of the physical activity programme. Furthermore, we hypothesise that early physical exercise programmes will lead to a reduction in sick leave and related production loss and that such programmes will be cost-effective. To study this hypothesis, we designed a randomised clinical trial: the Physical Activity during Cancer Treatment (PACT) study. In this manuscript, we describe the design and methods of the PACT study.

## Methods/Design

### Design

The PACT-study examines the effects of exercise during cancer treatment on reducing complaints of fatigue and in reducing health service utilisation and sick leave (primary outcomes). In addition, we will study the effects on improving health related quality of life, impact on autonomy and participation, anxiety and depression, physical fitness, body composition and cognitive-behavioral aspects (secondary outcomes). This study is designed as a multicentre pragmatic randomised controlled trial, with two study arms, i.e. a group invited for an exercise programme in addition to usual care; and the control group receiving usual care while maintaining their habitual physical activity pattern. The exercise programme is an 18-week supervised group programme. Because blinding of participants towards allocation is not feasible, this study has a pragmatic design.

### Subjects

A total of 300 newly diagnosed breast and colon cancer patients (150 per cancer type), who will receive adjuvant treatment, including chemotherapy, will be invited to participate in the PACT-study.

We decided to include patients diagnosed with breast and colon cancer, since these cancer types are among the most prevalent [13,14]. Inclusion criteria are: histological diagnosis of cancer less than six (breast cancer) or ten (colon cancer) weeks before study recruitment; stage M0; and scheduled for chemotherapy. Breast cancer patients with immediate use of a tissue expander after surgery may be included until ten weeks after histological diagnosis. They will start the exercise programme after replacement of the tissue expander by a breast prosthesis, since exercising with a tissue expander is discouraged by medical specialists. In agreement with the recommendations by the National Comprehensive Cancer Network, patients allocated to the exercise group will start shortly after diagnosis [6]. We decided to recruit patients scheduled for chemotherapy, because medical specialists frequently report fatigue in these patients. Some patients are also scheduled for radiotherapy preceding the chemotherapy. By choosing a more or less arbitrarily 18-week exercise programme, the programme in these patients will at least run during part of their chemotherapy treatment (see Figure 1).

**Figure 1 F1:**
[figure not shown]
**Interventions and timeline**.

Additional inclusion criteria are: age 25-75 years; not treated for cancer in the five years preceding recruitment (except basal skin cancer); able to read and understand the Dutch language; Karnovsky Performance Status of 60 or higher; able to walk 100 meter or more; no contra-indications for physical activity (assessed through the Revised Physical Activity Readiness Questionnaire).

Written informed consent will be obtained from all patients. This study has been approved by the Medical Ethics Committee of the University Medical Centre Utrecht and the local Ethical Boards of the participating hospitals.

### Recruitment and Allocation

Patients will be recruited by medical specialists and specialised nurses in at least six hospitals in the regions of the Comprehensive Cancer Centers Middle Netherlands, Limburg and Rotterdam. New cancer patients will be informed and invited by the clinician or the oncological nurse during a regular outpatient clinic visit. Patients willing to participate will be asked to visit the study centre to assess study eligibility and for baseline measurements. If eligible, patients will be asked to sign informed consent upon which they will be randomly allocated to the intervention or the control group by central data management. Allocation to the intervention- or control group will be concealed. Randomisation will be stratified per tumour site (breast or colon) by the sequential balancing method. The following characteristics will be balanced: age (25-40, 40-65 and 65-75 years), adjuvant treatment (radiotherapy versus no radiotherapy (before chemotherapy)); using a tissue expander (for breast cancer patients yes versus no) and hospital. For colon cancer patients, gender will be included as a first step in above balancing algorithm. Recruitment and allocation strategy is summarised in Figure 2.

**Figure 2 F2:**
[figure not shown]
**Planned inclusion and allocation of patients**.

### Exercise Intervention

The exercise programme is designed by applying the principles of 'Intervention Mapping' [15]. Intervention Mapping provides a framework for effective decision making in the developmental process of (health promotion) interventions using five steps: 1) specification of objectives, 2) development of methods and strategies, 3) design of the programme, 4) anticipation of implementation and 5) evaluation. The exercise objectives, specified for the specific target population were set by an in-depth literature search and by seeking advices of medical oncologists, radiotherapists and a surgeon. Subsequently, the exercise methods were developed in close cooperation with physiotherapists experienced in rehabilitation programmes for cancer survivors. This resulted in a clear exercise programme and materials for instruction for physiotherapists as well as information leaflets for patients. We continuously involved medical specialists and physiotherapists in the development in order to optimise implementation of the exercise programme in the health care system.

The exercise programme will be offered at several outpatient clinics of general hospitals. Participants will attend this programme twice a week. The programme incorporates principles for aerobic training and muscle strength training as well as principles of Bandura's social cognitive theory [16].

The programme will be individualised to the patient's personal preferences and physical fitness level. During an intake prior to the exercise programme, information about patient's preferences, regular sports activities, requirements at home and work, and physical fitness level (by means of a symptom limited exercise test and 1-repetition maximum (1-RM) muscle strength tests) and physical limitations will be collected by the physiotherapist. After the intake, the patient will start the 18-week exercise programme. The 1-hour exercise classes will include a warming up (5 min), aerobic and muscle strength training (50 min) and a cooling down (5 min). *Aerobic training *includes interval training of alternating intensity at or below the ventilatory threshold (3 × 2 min increasing to 2 × 7 min) as determined during the baseline symptom limited bicycle ergometry test (see study end points, secondary outcomes). Heart rate and the Borg scale of perceived exertion will be monitored during the aerobic training.

*Muscle strength training *will be performed for all major muscle groups: arms, legs, shoulders, and trunk: 2 × 10 repetitions (65% 1-RM) increasing to 1 × 10 repetitions (75% 1-RM) and 1 × 20 repetitions (45% 1-RM).

The exercise programme incorporates principles of Bandura's social cognitive theory (SCT) to help participants maintaining a physically active lifestyle during and after cancer treatment [16]. This theory emphasises the role of cognitive processes in determining behaviour such as exercise. The most important construct in the theory is self-efficacy that is defined as "an individual's beliefs in his/her capabilities to organise and execute the course of action required to produce given attainments" [16]. The concept has been used successfully in other intervention studies that aim to alter health related behaviour [17]. Self efficacy will be altered using three different techniques, namely actual or mastery experience, vicarious or observational experience and verbal persuasion. First, actual or mastery experience will be used by asking participants to report training results in graphs. Physiotherapists will check these weekly and give positive feedback about the obtained results and will stimulate the participant to make action plans to further increase their exercise level. The starting point of the training schedule has been carefully chosen so it will be likely that the participant will succeed and subsequently have a mastery experience in doing physical exercises.

Vicarious or observational experience is applied by using DVDs where other cancer patients show their experiences with exercise programmes. Also the use of a so-called buddy will help in role modelling as a component of the programme. The buddy is a senior participant introducing a new participant to the programme. During the programme they will work together and support each other when facing difficulties in executing the exercises. Finally, verbal persuasion is used. Physiotherapists will strongly recommend exercise which will be supported by written information.

In addition to the supervised exercise programme twice a week, patients are recommended to be physically active for at least 30 minutes a day, five days a week according to the Dutch guideline for physical activity [18], which is based on international recommendations [19,20]. This should include an aerobic component of moderate intensity in agreement with the participant's fitness and desires.

